### Composition of the data monitoring committee, its role and reporting structure {21a}

Not applicable. In this study, no formal committees will be formed. The funding body has no role in the study design and the collection, analysis, interpretation, and presentation of the study data.

### Adverse event reporting and harms {22}

Adverse events, such as falls and injuries during training, will be recorded. The principal investigator will promptly consult the ethics committee and take appropriate action in response to any serious adverse events, regardless of their causal relationship with the intervention.

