## Introduction

### Background and rationale {6a}

Through attentional function, individuals select appropriate information from senses, memory, and thoughts. Attentional function forms the basis of various cognitive functions, including orientation, memory, and comprehension [1]. Attentional function is known to peak around the age of 20 and gradually decline with age [2, 3]. This decline leads to difficulties in instrumental activities of daily living (IADLs), such as managing finances [4] and performing laundry [5]. Furthermore, the decline is associated with an increased risk of falls [6, 7] and motor-vehicle accidents [8, 9]. Therefore, preventing the decline of attentional function is a crucial challenge for promoting independent living in older adults.

Dual-task training (DTT) is an intervention designed to enhance attentional control during multitasking. In this training, individuals are required to perform multiple tasks, such as motor and/or cognitive tasks, simultaneously. It has been reported to improve attentional impairments associated with cerebrovascular disorders and traumatic brain injury [10–12]. To maximize the effectiveness of DTT, task difficulty should be individually adjusted based on Dual-Task Interference (DTI) [12, 13]. In DTI, performance deteriorates when two tasks are performed simultaneously, even though each task is manageable when performed alone. Because the effectiveness of DTT is diminished when the level of interference is either too high or too low, an appropriate level should be identified for each individual.

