## Interventions

### Explanation for the choice of comparators {6b}

Through the trial, the attentional function of the intervention and control groups at baseline and post-intervention will be assessed to determine the effectiveness of DTT. The control group will consist of community-dwelling older adults living in the same area. They will continue their usual daily activities throughout the study period. As an ethical consideration, participants in the control group will have the opportunity to experience the DTT intervention after the study is complete.

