### Intervention description {11a}

The DTT consists of a combination of “motor tasks” and “cognitive tasks involving motor activity”, and task difficulty is individually adjusted based on DTI. The intervention will be conducted at the Health and Welfare Center in Kagamiishi Town. It will be delivered by two occupational therapists who are well-versed in DTT with the assistance of two volunteers for operational support. The intervention will be implemented twice per week for four weeks, with each session lasting one hour. To facilitate implementation in community settings, DTT will be conducted with a group of approximately 30 participants.

Each one-hour session consists of a 5-minute health check, 10-minute warm-up exercises, 15-minute DTT, a 10-minute break, another 15-minute DTT, and a 5-minute cool-down. The specific tasks used in the intervention are presented in Table 1. In the DTT, participants will first practice “motor tasks” and “cognitive tasks involving motor activity” as single tasks. After they are accustomed to performing each task individually, they will perform two tasks simultaneously.

**Table 1 Tab1:** Examples of DTT task combinations

Motor tasks [18, 21, 22]	Cognitive tasks involving motor activity
・Stepping in a seated position ・Stepping in a standing position	■Finger exercises [21, 25] ∙ Perform combinations of hand gestures, such as rock and paper, rock and scissors, and scissors and paper, with both hands ∙ Perform different hand gestures simultaneously with each hand, such as rock with one hand and paper with the other ∙ Perform complex bilateral movements, alternating between the extension of the thumb on the one hand and the extension of the little finger on the opposite hand
・Stepping in a seated position ・Stepping in a standing position	■Upper limb exercises [17, 18, 21] ∙ Move both upper limbs in the instructed direction ∙ Move both upper limbs in the opposite direction of the instruction ∙ Perform vertical movements with one upper limb and triangular movements with the other ∙ Switch the roles of the upper limbs midway through the task
・Stepping in a seated position ・Stepping in a standing position	■Exercises using tools [18] ∙ Toss and catch a beanbag with one hand ∙ Toss and catch one beanbag with both hands ∙ Toss and catch two beanbags simultaneously with both hands

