## Data collection and management

### Plans for assessment and collection of outcomes {18a}

All participants will be assessed on all outcome measures at baseline (T0) and at re-evaluation (T2). Prior to data collection, data collectors will receive sufficient training on measurement methods, including the TMT-J, the digit span test, the Stroop and reverse-Stroop test and the single-leg stance time with eyes open and closed. Collected data will be recorded on a record sheet displaying written results, and any missing or inconsistent data will be checked and corrected as necessary. All data will be checked for completeness and accuracy before being entered into a secure electronic database. Before statistical analysis, all data will be cleaned, outliers will be examined, and the normality of the distribution will be tested.

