## Oversight and monitoring

### Composition of the coordinating centre and trial steering committee {5d}

This is a single-centre study designed, implemented, and coordinated at Fukushima Medical University. Day-to-day support for the trial is provided by the following staff:Principal investigator: Supervises the trial, conducts trial registration and participant enrolment, obtains informed consent, and ensures that the follow-up is conducted in accordance with the protocol.Data manager: Organizes data acquisition and safeguards the quality of the data.Data collectors: Conduct data acquisition, including assessments of attention and balance functions.Statistician: analyzes data after trial completion.

The principal investigator, data manager, data collectors, and statistician will meet before, during, and after the trial.

In this study, no formal independent committees, such as a steering committee or a data monitoring committee, will be established owing to the fact that it is a single-centre study with a low-risk, non-invasive intervention.

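### The adverse event rule exemplifies only training events and states no equal ascertainment in the two arms, so non-serious falls and injuries may be captured unevenly

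*Protocol article*

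**What the plan says.** The protocol article covers harms in two sentences under Adverse event reporting and harms {22}. The first is the recording rule: "Adverse events, such as falls and injuries during training, will be recorded". The second concerns serious events: the principal investigator will consult the ethics committee and "take appropriate action in response to any serious adverse events, regardless of their causal relationship with the intervention".

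The arms differ in what happens between assessments. For the DTT arm, Intervention description {11a} states: "The intervention will be implemented twice per week for four weeks, with each session lasting one hour". Each session opens with a short health check. For controls, Explanation for the choice of comparators {6b} states: "They will continue their usual daily activities throughout the study period". It adds that "participants in the control group will have the opportunity to experience the DTT intervention after the study is complete", so controls do no training while the trial runs. Outcome assessment in both arms is at t0 and t2 only (Table 2 and {18a}).

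Falls also appear elsewhere. The rationale in {6a} says of attentional function that "the decline is associated with an increased risk of falls". Item {11a} provides for supports near participants during standing stepping, to prevent falls. Item {5d} gives as a reason for having no independent committee that "it is a single-centre study with a low-risk, non-invasive intervention".

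**The concern.** The only examples of recordable events belong to a setting that one arm lacks. A control who falls at home has had an adverse event in the ordinary sense, but nothing in the article tells staff to ask about it. The same holds for a DTT participant who falls on a day without a session. The data-collector training described in {18a} covers the outcome tests and does not mention asking about events.

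Two things are at stake. First, unequal opportunity to notice events tends to load them onto DTT, whatever the true rates. Second, a real excess or reduction in falls outside sessions could be missed, although the protocol itself treats falls as a consequence of attentional decline and as a risk of the exercise. If the results paper tabulates events by arm, the reader could not separate a difference in harm from a difference in asking. Analysis cannot repair this later, because events never asked about are not in the data.

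**Working it through.** Item {22} gives no figure to reproduce. The check sets the provisions side by side and then asks what the available numbers can show.

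**Opportunities to learn of an event between t0 and t2**

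- DTT arm: 2 sessions a week × 4 weeks = 8 planned contacts, each with a health check ({11a}).
- Control arm: 0 planned contacts ({6b}, Table 2, {18a}).
- At t2 itself: 1 visit in each arm, plus renewed contact with anyone unavailable ({18b}). The article does not say that adverse events are asked about there.

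**What each sentence of {22} covers**

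- *Recording rule.* It applies to adverse events generally; falls and injuries in training are examples. A fall at home, or during the single-leg stance test that both arms perform ({12}), is not excluded, but no example or instruction points to it.
- *Serious-event sentence.* It has no limit by arm or setting. It says what follows once an event is known, not how it becomes known, and it does not reach non-serious events.

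**Effect on a comparison by arm**

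Let the true number of non-serious events per arm be equal, and let c1 and c0 be the proportions that come to notice in the DTT and control arms. The expected ratio of recorded counts is c1/c0. It equals 1 only if c1 = c0. The article gives neither proportion and describes nothing that would make them equal. With 8 interim contacts against 0, c1 > c0 is the likelier direction.

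**How many events could be involved**

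The planned size is 60 at 1:1, so 30 per arm ({14}, {8}). The article gives no background event rate. Assuming that a proportion p of participants has a non-serious event in four weeks, the expected number per arm is 30 × p:

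- p = 2%: 30 × 0.02 = 0.6
- p = 5%: 30 × 0.05 = 1.5
- p = 10%: 30 × 0.10 = 3.0

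Over this assumed range only a few events per arm are in question, so missing one or two would change the picture visibly.

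**Supervised time**

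Session time is 8 × 1 h = 8 h. Four weeks are 28 × 24 = 672 h, and 8/672 = 1.2%. This is the share of elapsed time under supervision. It is not the share of events captured, because an event outside a session can be reported at the next contact.

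**The case against.** The strongest reply is that the recording rule is general and its examples are only examples. Followed as written, a control's fall is an adverse event and is to be recorded. The serious-event sentence supports this, since acting regardless of cause does not fit a scheme confined to sessions. Item {11b} also foresees hospitalization and physician-imposed restrictions, which arise outside sessions. Both arms are seen at t2, and the session health check lets DTT participants report events from the days between. How events are elicited is a detail that an article commonly leaves to the full protocol, and {31c} indicates that one exists. Finally, falls are not an outcome, no comparison of harms between arms is planned, and about 30 per arm over four weeks would give an imprecise one.

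Much of this stands. The examples are not a restriction, serious events are covered in both arms, and the lack of an elicitation procedure in an article would not by itself be a finding. What remains is narrower: the setting the rule does mention exists in one arm only, and the contact schedule favours the same arm. The health check, offered as a remedy, widens the imbalance, because controls have no counterpart. The t2 visit is common to both arms but is given no role in recording events. That no formal comparison is planned lowers the stakes without removing them, since events listed by arm invite comparison.

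**Conclusion.** The point holds as a weakness of wording and design that is cheap to remedy. As {22} stands, non-serious falls and injuries in controls, and those outside sessions in either arm, may go unrecorded, and counts by arm could not then be fairly compared. The size of the loss cannot be derived from the article. The facts are 8 planned interim contacts against 0; the number of events involved is probably small, on assumed rates. The conclusion assumes that the full protocol, which is not shown, adds no equal enquiry. The analyses of the Trail Making Test and the secondary outcomes are unaffected.

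A reader might infer more: that recording is confined to sessions, that controls are bound to show zero events, that the arms can never be compared, or that only 1.2% of events would be captured. The article supports none of these. Its examples leave other events recordable, serious events are acted on in either arm, and the 1.2% describes supervised time.

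**What to change.** State in {22} that adverse events are recorded in both arms, in and outside sessions, from t0 to t2. At the existing t2 visit, ask every participant the same short question about falls, injuries and medical visits since t0. Ask it after the outcome tests are completed, because an answer that mentions the sessions could reveal the allocation to a data collector who is meant to be blinded ({17a}). Report these events by randomised arm, and list events during sessions separately for the DTT arm, so that the equally ascertained events are not mixed with those that only one arm can have.

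The cost is about a minute per participant, a line on the record sheet and some recall error over the interval. Under {25} the change also needs ethics committee approval before use and a registry update. Recruitment began in August 2025, so any t2 visits already held without the question should be identified when the events are reported.

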### Frequency and plans for auditing trial conduct {23}

Not applicable. In this study, no external audit will be conducted.

### Plans for communicating important protocol amendments to relevant parties (e.g. trial participants, ethical committees) {25}

All protocol modifications will be submitted in writing to the ethics committee for review and approval prior to implementation. Each time an amendment is made, the online trial registry will be updated. All approved protocol amendments will be communicated to relevant stakeholders and investigators.

### Dissemination plans {31a}

The findings of this study, including both positive and negative results, will be published in a peer-reviewed journal. A summary of the research findings will be made available to participants upon request.

## Discussion

### Background and purpose

Attentional function is a fundamental component of various cognitive functions [1], and its decline has been associated with cognitive impairment and difficulties in performing IADLs [4, 5]. Moreover, attention decline is known to affect many aspects of daily life, including an increased risk of falls [6, 7] and a higher risk of motor-vehicle accidents [8, 9]. The above factors show that enhancing attentional function is crucial for enabling community-dwelling older adults to maintain healthy lives in their familiar environments.

Therefore, in the present study, we developed a DTT program with the aim of preventing attention decline and designed a research protocol to evaluate its effectiveness.

### Strengths of this study

The following are the main features of this study.Simplicity and Versatility: The DTT program is designed to be simple and versatile, requiring no large-scale equipment or special facilities, and can be easily implemented in daily life settings.Task Components: The program combines “motor tasks” and “cognitive tasks involving motor activity.” Further, task difficulty will be individually adjusted according to each participant, considering DTI. These two features contribute to an effective task design to enhance attentional function.Comprehensive Assessment of Attention: This study will be conducted to evaluate multiple aspects of attention, including sustained, selective, divided attention, and attentional capacity, using various measures such as TMT-A, TMT-B, digit span test, and the Stroop and reverse-Stroop test. These comprehensive assessments will be used to enable a more detailed examination of the effects of DTT on attentional function.

### Future directions

The DTT program developed in this study can be implemented regardless of time and place. In the future, its dissemination and integration into community gatherings and preventive care services for older adults may be promoted through brochures and instruction manuals. This approach is expected to promote the maintenance and improvement of attentional function among community-dwelling older adults, ultimately contributing to the extension of healthy life expectancy and the enhancement of their quality of life.

## Trial status

Trial registration: UMIN, UMIN000057681. (Registered 30 June 2025).

UMIN website https://center6.umin.ac.jp/cgi-open-bin/ctr/ctr_view.cgi?recptno=R000065882

(Version 1.0 dated 30 June 2025)

The data recruitment began in August 2025, and recruitment will be completed on 25 September 2025.

## Data Availability

The authors will have access to the final trial dataset. Statisticians responsible for outcome analysis will be provided with the complete dataset once data collection is complete. Data required to support the protocol will be made available upon request. However, access to the data by individuals who have not been approved by the ethics committee may require additional ethical approval.

## Abbreviations

DTI: Dual-task interference
DTT: Dual-task training
TMT-J: Trail Making Test-Japanese
TMT-A: Trail Making Test-Japanese part A
TMT-B: Trail Making Test-Japanese part B
IADLs: Instrumental activities of daily living
